#### Secondary outcomes

2.6.2

(1) Exhaled carbon monoxide (CO) as a continuous measure will be assessed at all visits to reflect recent smoking behavior (34).(2) Point prevalence abstinence at week 24 will be assessed as a secondary time point using the same definition as the co-primary PPA outcome (self-report + CO < 6 ppm) (33, 35).(3) Quality of life will be assessed using the validated Chinese version of the Short Form 36 Health Survey (SF-36), which includes eight domains of physical and mental health (36).(4) Sleep quality will be assessed using the Chinese version of the Pittsburgh Sleep Quality Index (PSQI) (37).(5) Depressive symptoms will be assessed using the Beck Depression Inventory-II (BDI-II) (38).(6) Anxiety symptoms will be assessed using the Beck Anxiety Inventory (BAI) (39).

Assessment time points for all outcomes are summarized in Table 1.

### Safety assessments and adverse events

2.7

#### Safety parameters

2.7.1

Safety assessments will include hematological, hepatic, renal, inflammatory, and cardiac parameters. Hematological tests will include white blood cell count, hematocrit, hemoglobin, and platelet count. Liver function will be assessed using aspartate aminotransferase (AST), alanine aminotransferase (ALT), and gamma-glutamyl transferase (GGT). Values exceeding three times the upper limit of normal (ULN) will prompt clinical evaluation. Renal function will be assessed using serum creatinine and blood urea nitrogen (BUN). Inflammatory status will be evaluated using erythrocyte sedimentation rate (ESR). Cardiac safety will be assessed using a standard 12-lead electrocardiogram (ECG) at baseline and after treatment completion (40).

#### Adverse events reporting

2.7.2

Adverse events (AEs) will be defined as any untoward medical occurrences during the study, regardless of their causal relationship with the intervention. All AEs will be recorded in case report forms (CRFs), including onset time, clinical features, severity (mild, moderate, or severe), duration, management, and outcome. Serious adverse events (SAEs), including death, life-threatening events, hospitalization or prolonged hospitalization, significant disability, or congenital anomalies, will be reported to the institutional ethics committee within 24 h. The committee will review each SAE and determine whether protocol modifications or trial discontinuation are required.

#### Ongoing safety monitoring

2.7.3

Safety monitoring will be conducted throughout the study. Decisions regarding participant withdrawal for safety reasons will be made by the principal investigator in consultation with the research team. Safety data will be reviewed regularly by an independent data monitoring committee. A summary of AEs during the treatment phase will be presented in Table 4.

**Table 4 tab4:** Adverse events and side effects monitoring.

Date	Patient ID	Adverse event	Severity	Outcome	Duration	Action taken	Follow-up and remarks
							
							
							
							

Template for recording adverse events during the study; this table will be completed after trial initiation and during study conduct.

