**Methods:**

This is a single-center, pragmatic, randomized, parallel-group controlled trial. A total of 220 participants with TUD will be randomly assigned (1,1) to receive either harmonizing mind acupuncture (HMA) plus NRT or NRT alone. The intervention period will last 6 weeks, with follow-up to 24 weeks. The co-primary outcomes are: (1) the change in nicotine craving measured by a visual analog scale (VAS) from baseline to week 6; and (2) 7-day point prevalence abstinence (PPA) biochemically verified by exhaled carbon monoxide at week 6. Secondary outcomes include exhaled carbon monoxide (as a continuous measure), quality of life, sleep quality, depressive symptoms, anxiety symptoms, and safety outcomes. Analyses will be conducted according to the intention-to-treat principle.

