### Study design and setting

2.1

This study is a pragmatic, randomized, single-center, parallel-group clinical trial designed to evaluate the effectiveness and safety of HMA as an adjunct to NRT in individuals with TUD.

The study has been approved by the Ethics Committee of the Affiliated Hospital of Yunnan University (approval number: KJR#20251111-R1-055) and registered with the International Traditional Medicine Clinical Trial Registry (ITMCTR2026000683). The protocol was developed in accordance with the SPIRIT 2013 guidelines and the Standards for Reporting Interventions in Controlled Trials of Acupuncture (STRICTA) recommendations (13–15). Written informed consent will be obtained from all participants prior to enrollment.

An overview of the trial flow is presented in Figure 1, and the schedule of enrollment, interventions, and assessments is shown in Table 1. This study is designed to assess the real-world effectiveness of HMA when used alongside standard nicotine replacement therapy in routine clinical practice.

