**Figure 1 fig1:**
[figure not shown]
Flowchart of the pragmatic randomized controlled trial evaluating HMA combined with NRT. This diagram outlines the study design and procedural timeline, including screening, random allocation to two groups (HMA + NRT vs. NRT alone), the intervention schedule, assessment time points, and follow-up. The co-primary outcomes are: (1) change in nicotine craving intensity assessed by the visual analog scale (VAS) from baseline to week 6; and (2) 7-day point prevalence abstinence (PPA) at week 6 biochemically verified by exhaled carbon monoxide. Secondary outcomes include exhaled carbon monoxide (as a continuous measure), quality of life (SF-36), sleep quality (PSQI), depressive symptoms (BDI-II), and anxiety symptoms (BAI). Safety monitoring, including adverse event (AE) reporting and clinical evaluations, is conducted throughout the trial.

**Table 1 tab1:** Participant flow and study timeline.

Timepoint (week)	-1	0	2	4	6	10	24
Enrollment phase							
Screening	×						
Informed Consent		●					
Allocation		●					
Intervention phase							
HMA + NRT Group		●	●	●	●		
NRT-only Group (+ health education for attention control)		●	●	●	●		
Assessment phase							
VAS (Nicotine Craving) (Co-primary outcome)		●	●	●	●	●	●
PPA (7-day Point Prevalence Abstinence) (Co-primary outcome)					●		●
CO (Exhaled Carbon Monoxide)		●	●	●	●	●	●
SF-36 (Quality of Life)		●		●	●	●	●
PSQI (Sleep Quality)		●		●	●	●	●
BDI-II (Depression Symptoms)		●		●	●	●	●
BAI (Anxiety Symptoms)		●		●	●	●	●
Safety monitoring							
Adverse events		●	●	●	●	●	●

This table presents a detailed overview of the study schedule, including participant enrollment, administration of interventions (HMA plus NRT or NRT alone), assessment timepoints for outcome measures, and safety monitoring (adverse events). Black dots (●) indicate the scheduled activities at each timepoint. The co-primary outcomes are: (1) change in VAS from baseline to week 6; and (2) 7-day point prevalence abstinence (PPA) at week 6.

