### Interventions

2.4

Acupuncture interventions will be delivered by licensed acupuncturists with at least 3 years of clinical experience. The HMA protocol is based on classical meridian theory and adapted from prior randomized controlled trials, with refinement by a panel of senior experts. All practitioners will undergo standardized training before trial initiation, and a detailed procedural manual will be provided to ensure protocol adherence and minimize inter-operator variability.

Participants in the intervention group will receive HMA in addition to a standardized NRT regimen (identical to the control group). Acupuncture sessions will last approximately 30 min and will be administered three times per week for 6 weeks (total of 18 sessions). The control group will receive NRT alone. Following the treatment phase, participants will enter a follow-up period with assessments at Weeks 10 and 24. The intervention schedule is summarized in Table 1, with detailed acupuncture procedures provided in Tables 2, 3 and Figure 2. All participants will receive standardized brief behavioral counseling consistent with clinical smoking cessation guidelines (24).

**Table 2 tab2:** HMA Acupuncture point grouping and functional classification.

Group	Acupuncture point	Code	Description
Central regulation	Baihui	GV20	At the intersection of the midline of the head and the line connecting the apexes of both ears.
	Shenting	GV24	0.5 cun directly above the midpoint of the anterior hairline.
	Yintang	GV29 (EX-HN3, also referred to as GV29)	At the glabella, the midpoint between the medial ends of the two eyebrows, on the anterior midline of the head.
Emotional modulation	Neiguan	PC6	2 cun above the transverse crease of the wrist, between the tendons of palmaris longus and flexor carpi radialis.
	Shenmen	HT7	At the ulnar end of the transverse crease of the wrist, in the depression on the radial side of the tendon of flexor carpi ulnaris.
	Sanyinjiao	SP6	3 cun directly above the tip of the medial malleolus, posterior to the medial border of the tibia.
Systemic support	Zusanli	ST36	3 cun below ST35, one finger breadth from the anterior crest of the tibia, in the tibialis anterior muscle.
	Hegu	LI4	On the dorsum of the hand, between the 1st and 2nd metacarpal bones, at the midpoint of the 2nd metacarpal bone on the radial side.

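### The only adverse event summary the protocol names stops at the treatment phase and points to a blank event log, although adverse events are collected to week 24

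*Protocol article*

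**What the plan says.** Safety is part of the aim. Section 2.1 describes the trial as "designed to evaluate the effectiveness and safety of HMA as an adjunct to NRT in individuals with TUD", and the abstract's list of secondary outcomes ends with "quality of life, sleep quality, depressive symptoms, anxiety symptoms, and safety outcomes".

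On when AEs are observed, the article is consistent. Section 2.7.3 states: "Safety monitoring will be conducted throughout the study". The Figure 1 legend agrees: "Safety monitoring, including adverse event (AE) reporting and clinical evaluations, is conducted throughout the trial". Table 1 marks AEs at weeks 0, 2, 4, 6, 10 and 24. Section 2.4.3 has AE diaries reviewed at those same six visits in both arms.

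On what will be presented, section 2.7.3 states: "A summary of AEs during the treatment phase will be presented in Table 4". Table 4 is an empty grid with one row per event. Its columns are date, patient ID, event, severity, outcome, duration, action taken, and follow-up and remarks. Its note reads: "Template for recording adverse events during the study; this table will be completed after trial initiation and during study conduct".

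Section 2.7.2 has all AEs recorded in the CRF, "including onset time, clinical features, severity (mild, moderate, or severe), duration, management, and outcome". Section 2.10 names no AE analysis, so the sentence in 2.7.3 is the only AE summary the article specifies.

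**The concern.** The collection window and the summary window differ. AEs are gathered for 24 weeks, but the one named summary covers the treatment phase, which is 6 weeks. This is more than detail left to an analysis plan, because the article commits to a window that leaves out part of its own schedule. Section 2.7.3 also gives Table 4 two roles: a summary of treatment-phase events in the text, and a recording form for the whole study in the note.

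If the sentence is followed, events that start or are found after week 6 are collected without any stated place in the results. A per-event listing also does not give the number of participants with an event in each arm, which is what a reader needs to judge the safety of adding harmonizing mind acupuncture (HMA) to nicotine replacement.

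A second matter bears on how the summary should be built. HMA participants attend 18 acupuncture sessions that controls do not. Reactions may be noticed there, and the article does not say how such reports are to be kept apart from events found at the visits both arms attend.

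**Working it through.** The plan gives no safety figure to reproduce beyond its session count. The check sets the passages side by side and counts from the plan's own schedule.

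**Windows**

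| Source | What it covers | Period |
|---|---|---|
| 2.7.3, monitoring sentence | Monitoring | Whole study |
| Figure 1 legend | Monitoring and AE reporting | Whole trial |
| Table 1, AE row | Collection | Weeks 0, 2, 4, 6, 10, 24 |
| Table 4 note | Recording | Whole study |
| 2.7.3, summary sentence | Presentation | Treatment phase (6 weeks) |

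Four entries agree; the summary sentence is the exception.

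**What falls outside the summary**

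- Scheduled AE assessments: 6. After the treatment phase: weeks 10 and 24, so 2 of 6. Leaving out baseline, 2 of 5.
- Study time: 24 − 6 = 18 weeks; 18/24 = 75%.

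**Contacts and scheduled AE assessments**

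- Acupuncture sessions (2.4): 3 per week × 6 weeks = 18, which agrees with the stated total.
- Treatment-phase visits in both arms (2.4.3, Table 1): weeks 0, 2, 4 and 6 = 4.
- HMA contacts in the treatment phase: 18 if every visit falls on a session day, 18 + 4 = 22 if none does. Control contacts: 4. Ratio 18/4 = 4.5 to 22/4 = 5.5.
- The control arm's health education (2.4.4) is given at the existing visits and adds none.
- Scheduled AE assessments: 4 against 4 in the treatment phase and 6 against 6 overall.

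The stated AE route is therefore balanced between arms. Opportunity for unscheduled reporting is not. Section 2.4.1.3 has the acupuncturist deal with reactions at sessions, and 2.7.2 requires all AEs to be recorded, so such events may reach the CRF through a route that controls do not have. The documents give no reporting rates, so the effect on AE counts cannot be sized.

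**The case against.** The strongest reply is that Table 4 is, by its own note, a recording template, and that the sentence promises a summary without calling it the only safety output. All AEs go into the CRF, laboratory tests and ECG are planned, and an independent committee reviews safety data. Tables by arm are commonly left to a full protocol or analysis plan that is not shown. Acupuncture and patches are both given only in weeks 0–6, so treatment-related events should concentrate there.

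Much of this stands, and it rules out several stronger readings:

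- A reader might infer that the trial cannot meet its safety aim. The documents do not support that, because the data are collected and reviewed.
- A reader might count the absence of an arm column in Table 4 as a defect. Patient ID links each event to its randomised arm, and leaving arm off a working log fits with blinded data staff.
- A reader might infer that HMA event counts will be inflated by the extra sessions. The stated route is diary review at common visits, and nothing says AEs are solicited at sessions. Unequal spontaneous reporting is a possibility to guard against and is not something the plan prescribes.
- A reader might infer that relatedness is not recorded. The field list in 2.7.2 opens with a word that need not make it exhaustive.

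What the reply does not remove is the mismatch itself. The article states a presentation window narrower than its collection window, and an unseen document cannot be assumed to override that.

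**Conclusion.** The point holds as a reporting mismatch that should be corrected. As written, two of six scheduled AE assessments, spanning 18 of 24 weeks, lie outside the only named AE summary, and that summary is assigned to a form built for recording single events. The 75% is a share of calendar time; the share of events is unknown and may well be smaller.

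This rests on reading the treatment phase as weeks 0–6, as Table 1 and section 2.4 indicate, and on no other AE summary being specified in the article. The co-primary analyses are not affected. The advice on session-noted reactions is a precaution that follows from the 18 additional contacts. The relatedness field is secondary and would support the summary.

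**What to change.** Replace the summary sentence in section 2.7.3 with: *AEs and SAEs from randomisation to week 24 will be summarised by arm (participants with at least one event, by severity), separately for weeks 0–6 and after week 6.* The CRF already records onset time, so events can be assigned to a period by onset. Describe Table 4 in the text as a recording log only, in line with its note.

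Add that the comparison between arms uses AEs elicited by diary review at the common visits, and that reactions noted at acupuncture sessions are reported separately for the HMA arm. This needs a CRF field for where the event was reported. State whether the CRF records relatedness, and add the field if it does not; it is best settled before enrolment, because a judgement made at the time of the event is hard to reconstruct later.

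The cost is minor wording and one or two CRF fields. No visits or participants are added.

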### Quality control, data management, and monitoring

2.8

Before participant enrollment, all study personnel will undergo standardized training to ensure adherence to the study protocol and operational procedures. Acupuncture treatments will be delivered by licensed acupuncturists with at least 3 years of clinical experience. A detailed protocol handbook, including stepwise HMA procedures and standardized operating procedures (SOPs), will be provided to ensure consistency in intervention delivery (41).

Clinical data will be collected using predesigned case report forms (CRFs) and entered into a secure, password-protected electronic data management system. Data entry will be performed by trained personnel blinded to group allocation. Double data entry and independent verification will be conducted to ensure data accuracy and completeness. Real-time validation checks and regular audits will be performed by certified clinical research associates.

All original CRFs and source documents will be securely stored at the Affiliated Hospital of Yunnan University in accordance with Good Clinical Practice (GCP) standards. Oversight and monitoring will be conducted by the hospital’s Clinical Research Unit, which operates independently of the study investigators and funding sources. On-site monitoring visits will be conducted quarterly to assess protocol adherence. The Clinical Research Unit may suspend or terminate the study in the event of major protocol violations, safety concerns, or significant data inconsistencies.

### Patient and public involvement

2.9

Patients and/or the public were not involved in the design, conduct, reporting, or dissemination of this research.

### Statistical analysis

2.10

An independent statistician contributed to the development of the statistical analysis plan and the sample size calculation. This statistician, who will remain blinded to group allocation and not involved in study conduct, will perform all analyses according to the pre-specified plan. All analyses will be conducted according to the intention-to-treat (ITT) principle, including all randomized participants in their assigned groups.

#### Two co-primary outcomes will be analyzed as follows

2.10.1

Multiplicity control for co-primary outcomes. Type I error is controlled at the family-wise level using the Hochberg procedure. The trial will be declared positive only if both co-primary outcomes (VAS craving change and PPA at week 6) achieve statistical significance at *p* ≤ 0.05.

The change in nicotine craving intensity measured by the VAS from baseline to week 6 (one of the two co-primary outcomes) will be analyzed using linear mixed-effects models including fixed effects for group, time, and group × time interaction, with participant-specific random intercepts to account for repeated measurements.

The PPA at week 6 (the second co-primary outcome) will be analyzed using generalized estimating equations (GEE) with a logit link function and an exchangeable correlation structure. Results will be reported as adjusted odds ratios (ORs) with 95% confidence intervals (CIs).

For smoking abstinence outcomes, missing smoking-status data will be treated as non-abstinent in the primary analysis. For sensitivity analysis, a pattern mixture model under missing-not-at-random (MNAR) assumptions will be applied, assuming a relapse rate of 80–90% among participants with missing follow-up data (42).

Secondary continuous outcomes will be analyzed using linear mixed-effects models, including fixed effects for group, time, and group × time interaction, and random intercepts to account for within-subject correlation. Models will be adjusted for baseline values where appropriate. SF-36 total scores and PSQI global scores will be analyzed directly, with similar models applied to BDI-II, BAI, and exhaled carbon monoxide (CO).

To control for type I error due to multiple comparisons across the secondary outcomes (BDI-II, BAI, SF-36, PSQI, CO), a false discovery rate (FDR) procedure will be applied. Adjusted *p*-values will be reported alongside unadjusted estimates, and findings will be interpreted with appropriate caution (43).

Prespecified subgroup analyses will include three-way interaction terms (subgroup × treatment × time) within mixed-effects models to explore potential effect modification by sex (male/female) and age (<40 vs. ≥40 years).

Sensitivity analyses will include a per-protocol (PP) analysis excluding participants with less than 80% adherence, defined as attendance at fewer than 14 of 18 acupuncture sessions or NRT use on fewer than 80% of study days.

Between-group differences in clinical contact and expectancy scores will be explored and adjusted for in sensitivity analyses to account for attention-related effects (16).

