The sample size was calculated based on the co-primary outcome of 7-day point prevalence abstinence (PPA) at week 6. Referring to recent systematic reviews of acupuncture smoking cessation trials (21, 22), a control group abstinence rate of approximately 15% was assumed, with an odds ratio (OR) of 1.9 for the HMA + NRT group. With a two-sided significance level of *α* = 0.05, 80% power, and a 1:1 allocation ratio, a total of 188 participants is required. Accounting for a 15% dropout rate, the final sample size is set at 220 participants (110 per group) (23). The VAS craving outcome, as the other co-primary endpoint, is also adequately powered based on the same sample size. Multiplicity control. Because two co-primary outcomes are designated, the overall type I error rate is controlled using the Hochberg procedure. Under this approach, each outcome is tested at the full *α* = 0.05 level; the family-wise error rate is preserved because the trial is considered positive only if both co-primary outcomes achieve statistical significance (*p* ≤ 0.05 each). This method offers greater power than Bonferroni correction while maintaining strong control of the family-wise error rate.

To monitor expectancy and attention effects, participants will complete the Credibility/Expectancy Questionnaire (CEQ) at baseline and post-randomization; these scores will be explored in sensitivity analyses (16).

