#### Adherence monitoring and data collection

2.4.3

Participants will attend six in-person visits (baseline and Weeks 2, 4, 6, 10, and 24). Each visit will include:

(1) Compliance assessment: NRT patch verification and diary review (VAS scores and adverse events).(2) Outcome assessments (Table 1):

- CO and VAS: all visits.- PPA: Weeks 6 and 24.- SF-36, PSQI, BDI-II, and BAI: baseline and Weeks 4, 6, 10, and 24.

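### The co-primary craving model omits baseline VAS as a covariate and has only a random intercept, which costs precision and may misstate the week-6 standard error

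*Protocol article*

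**What the plan says.** Section 2.6.1 defines the first co-primary outcome as the change in VAS craving between baseline and week 6. Section 2.10.1 analyses it with "linear mixed-effects models including fixed effects for group, time, and group × time interaction, with participant-specific random intercepts to account for repeated measurements". That sentence lists no baseline covariate, no constraint on the baseline means, no other covariance structure and no robust standard error.

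Baseline adjustment appears further down the same section, in the paragraph on secondary continuous outcomes: "Models will be adjusted for baseline values where appropriate". Nothing extends it to the co-primary VAS model.

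Section 2.4.3 sets six visits (weeks 0, 2, 4, 6, 10 and 24) and collects "CO and VAS: all visits". The article does not say which of these visits enter the co-primary model, nor whether week 0 is a response or serves only to form change scores.

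**The concern.** Two things follow from the model as written.

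First, with week 0 in the response and a free group effect, the group × time contrast at week 6 subtracts baseline with a fixed weight of one. The better weight is the regression of week 6 on baseline, which is usually below one. The cost is precision, although the baseline value is already collected. As written, a co-primary endpoint gets a less efficient model than the one allowed for the secondary outcomes.

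Second, a random intercept alone assumes one variance at every visit and one correlation for every pair of visits. The visits are unevenly spaced and span quitting, treatment and follow-up, so neither assumption is secure. Where it fails, the standard error of the week-6 contrast reflects an average over all modelled visits and not the baseline and week-6 pair on which the endpoint rests.

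The trial counts as positive only if both co-primary outcomes are significant, so lost precision or a wrong standard error on VAS bears on the trial's conclusion.

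**Working it through.** **The plan's own figures.** There is none for VAS: section 2.3 asserts adequate power without an SD, an effect or a correlation. The stated size rests on abstinence: "a control group abstinence rate of approximately 15% was assumed", "with an odds ratio (OR) of 1.9 for the HMA + NRT group", and "80% power, and a 1:1 allocation ratio, a total of 188 participants is required". The odds are 1.9 × 0.15/0.85 = 0.335, hence 25.1% in the HMA arm. The usual pooled formula at two-sided 0.05 and 80% power then needs 492 in total, not 188, and 94 per arm gives about 41% power. So 188 is not reproduced, but this concerns abstinence and has no bearing on the VAS model. Below, 94 per arm serves only as the number analysed.

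**Notation.** S00 and S66 are the VAS variances at weeks 0 and 6, S06 is their covariance and ρ their correlation. None is given in the article; all values below are assumptions.

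**Step 1: precision, complete data, week 0 in the response.**
- Change-score contrast: variance proportional to S00 + S66 − 2·S06.
- Baseline-adjusted contrast: variance proportional to S66 − S06²/S00.
- Difference: S00 − 2·S06 + S06²/S00 = (S00 − S06)²/S00, which is never negative. Apart from the small cost of estimating the slope, adjustment cannot lose.

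With equal SDs the ratio of adjusted to change-score variance is (1 − ρ²)/[2(1 − ρ)] = (1 + ρ)/2. Its inverse is the factor in sample size.

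| ρ | adjusted / change variance | extra patients needed by change scores | excess in SE |
|---|---|---|---|
| 0.3 | 0.65 | 54% | 24% |
| 0.5 | 0.75 | 33% | 15% |
| 0.6 | 0.80 | 25% | 12% |
| 0.8 | 0.90 | 11% | 5% |

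As an illustration, take an assumed effect of 0.42 SD with 94 per arm. Power for the change-score and the adjusted analysis is 68% and 86% at ρ = 0.3, 82% and 91% at ρ = 0.5, and 96% and 98% at ρ = 0.7.

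**Step 2: standard error under a random intercept only.** The true variance of the week-6 contrast is proportional to S00 + S66 − 2·S06. The model-based variance is proportional to 2 × (mean visit variance − mean between-visit covariance), averaged over the visits in the model. With equal SDs the ratio of model SE to true SE is √[(1 − mean correlation)/(1 − ρ)].

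- *Too small.* Correlation 0.8 between neighbouring visits, decaying by visit, six visits: mean correlation 0.616, ρ = 0.8³ = 0.512. Ratio √(0.384/0.488) = 0.89; actual two-sided type I error about 8%.
- *Too large.* Correlation 0.9 per two weeks, decaying with time, six visits: mean correlation 0.643, ρ = 0.9³ = 0.729. Ratio √(0.357/0.271) = 1.15; type I error about 2.4%.
- *Correct.* Constant correlation with equal SDs, or only weeks 0 and 6 in the model: ratio 1.00.

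Over a wider set of assumed covariances (serial decay, random slopes; SDs equal, rising, falling or smaller at baseline) the ratio runs from about 0.85 to 1.21 with all six visits, a type I error of about 10% down to 2%. With weeks 0 to 6 only, it runs from 0.76 to 1.06, about 14% down to 4%.

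**The case against.** A condensed article may leave full covariate lists to the analysis plan, and a random-intercept model is a recognised analysis, not an error. That is fair. But the article does more than stay silent: it spells out the co-primary model and places baseline adjustment with the secondary outcomes alone.

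It can also be said that no size comes from the documents. That stands. The gain from adjustment is small if ρ is high (5% in SE at ρ = 0.8), and the direction of any SE error is unknown. The abstinence endpoint may well limit the trial's chance of success more than VAS does.

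Three stronger readings are tempting, and the text does not support them.
- A reader might infer that the model runs over visits out to week 24. The schedule shows when VAS is measured; the model text names no window. The SE problem does not need week 24, since it can also arise with weeks 0 to 6.
- A reader might infer that an overall group × time test decides the endpoint. Nothing says so. The endpoint is consistently the change to week 6, which the model can supply as a contrast.
- A reader might infer that baseline is ignored altogether. If week 0 is in the response, the contrast already subtracts it. What is absent is a baseline covariate or equal baseline means.

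**Conclusion.** The point holds as a weakness in efficiency and in the standard error, not as a bias: with complete data the estimated week-6 difference is unaffected.

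The loss of precision is algebraic if week 0 is a response; its size depends on ρ, which the article does not give. With equal SDs and ρ between 0.3 and 0.8, the change-score contrast needs between 54% and 11% more patients for the same precision.

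The standard-error problem is conditional. It arises only if visits beyond baseline and week 6 are modelled and compound symmetry fails. The range of 0.85 to 1.21 shows what is possible under assumed covariances; it does not predict this trial's data. A shortfall in VAS power is not demonstrated, because its inputs are not stated.

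**What to change.** Rewrite the VAS paragraph of section 2.10.1, and any analysis plan, before unblinded analysis:
- Model post-baseline VAS with baseline VAS as a covariate, or keep baseline in the response and constrain the two group means to be equal there.
- Use categorical visit and group × visit, and state which visits enter.
- Use an unstructured within-person covariance, with a stated fallback if it does not converge (for example heterogeneous Toeplitz) or robust standard errors.
- Take the adjusted group difference at week 6 as the co-primary test.

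No new data are needed. With five post-baseline visits, an unstructured matrix has 5 × 6/2 = 15 parameters against 2 for a random intercept with residual variance, which 220 participants can support.
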